# Efficacy and safety of proxalutamide (GT0918) in severe or critically ill patients with COVID-19: study protocol for a prospective, open-label, single-arm, single-center exploratory trial

**DOI:** 10.1186/s40360-023-00678-7

**Published:** 2023-06-15

**Keywords:** COVID-19, Critical ill COVID-19, Proxalutamide, Severe COVID-19

## Abstract

**Background:**

The rapid worldwide spread of COVID-19 has caused a global health challenge with high mortality of severe or critically ill patients with COVID-19. To date, there is no specific efficient therapeutics for severe or critically ill patients with COVID-19. It has been reported that androgen is related to severe acute respiratory syndrome coronavirus 2 (SARS-CoV-2) infection. Proxalutamide as an androgen receptor antagonist has shown potential treatment effects on COVID-19 patients. Thus, this trial is designed to investigate the efficacy and safety of proxalutamide in severe or critically ill patients with COVID-19.

**Methods:**

This single-arm, open-label, single-center prospective exploratory trial is planned to recruit 64 severe or critically ill patients with COVID-19 in China. Recruitment started on 16 May 2022 and is foreseen to end on 16 May 2023. Patients will be followed-up until 60 days or death, whichever comes first. The primary outcome is the 30-day all-cause mortality. Secondary endpoints included 60-day all-cause mortality, rate of clinical deterioration within 30 days after administration, time to sustain clinical recovery (determined using an 8-point ordinal scale), mean change in the Acute Physiology and Chronic Health Evaluation II scores, change in oxygenation index, changes in chest CT scan, percentage of patients confirmed negative for SARS-CoV-2 by nasopharyngeal swab, change in Ct values of SARS-CoV-2 and safety. Visits will be performed on days 1 (baseline), 15 or 30, 22, and 60.

**Discussion:**

The trial is the first to investigate the efficacy and safety of proxalutamide in severe or critically ill patients with COVID-19. The findings of this study might lead to the development of better treatment for COVID-19 and provide convincing evidence regarding the efficacy and safety of proxalutamide.

**Trial registration:**

This study was registered on 18 June 2022 at the Chinese Clinical Trial Registry (ChiCTR2200061250).

## Background

In 2019, a novel coronavirus called severe acute respiratory syndrome coronavirus 2 (SARS-CoV-2) caused the COVID-19 pandemic outbreak, which turned into a massive global health challenge. According to the weekly epidemiological updates of the World Health Organization till 24 May 2023, approximately 766 million cases were confirmed worldwide, resulting in about 6.9 million deaths [1]. The clinical features of COVID-19 are diverse and range from asymptomatic to death, and severe and critically ill patients represented 14% and 5%, respectively [2]. The mortality for critical cases reached 60.5% according to a recent report [3]. Currently, in patients with moderate to severe COVID-19, the major available therapeutics are drug treatments, including antiviral agents, inflammation inhibitors/antirheumatic drugs, hyperimmune immunoglobulins, and so on. However, most studies of existing drug therapy have limited therapeutic effects and lack compelling evidence [4–6]. A systematic review of the antiviral drug remdesivir for patients with severe COVID-19 found that given the current evidence, the efficacy data of remdesivir in severe COVID-19 is insufficient [7]. Therefore, it is urgently necessary to identify an effective drug to combat the disease considering the grim situation.

Infections by the SARS-CoV-2 are dependent on transmembrane protease serine 2 (TMPRSS2) and host proteins angiotensin-converting enzyme 2 (ACE2) receptor [8]. It has been demonstrated androgen are the only known transcription promoters for the TMPRSS2 gene [9]. Moreover, it has also been shown that ACE2 activity reduction is associated with androgen decrease [8]. Several studies showed that androgen-mediated androgenetic alopecia (AGA) was associated with more severe COVID-19 diseases, which has been demonstrated in several studies in hospitalized men patients [10–12]. Thus, androgen plays a crucial role in SARS-CoV-2 infection and the androgen receptor (AR) blockers would likely improve the treatment effect of COVID-19.

Proxalutamide is a potent second-generation nonsteroidal androgen receptor antagonist, which has a better therapeutic effect than other antiandrogen compounds (bicalutamide and enzalutamide) [13, 14]. Previous studies also reported the use of proxalutamide in COVID-19. In a double-blinded, placebo-controlled, randomized clinical trial, females treated with proxalutamide have reduced hospitalization rates [15]. In another study in patients with mild to moderate COVID-19, proxalutamide significantly accelerates viral clearance and reduces the time to clinical remission [16]. However, most existing studies on proxalutamide in COVID-19 have focused on patients with mild to moderate [15–17]. There are no studies on the efficacy and safety of proxalutamide in the treatment of severe or critically ill patients with COVID-19. Therefore, a single-arm, open-label, single-center prospective exploratory trial is designed to investigate the efficacy and safety of proxalutamide in the treatment of severe or critically ill patients with COVID-19 in China.

## Methods

### Study design

This is a single-arm, open-label, single-center prospective exploratory trial to assess the efficacy and safety of proxalutamide in severe or critically ill COVID-19 subjects. Recruitment started on 16 May 2022 and is foreseen to end on 16 May 2023. This trial is designed according to the Standard Protocol Items: Recommendations for Interventional Trials (SPIRIT) 2013 Statement [18]. In addition, this trial is registered in the China Clinical Trial Registry (ChiCTR2200061250).

### Trial setting

The trial is being conducted in the Gerontology Center of Zhongshan Hospital affiliated to Fudan University. The center is a 2000-bed tertiary general hospital located in Shanghai, China, which is a temporarily designated hospital for the treatment of patients with COVID-19 during the COVID-19 pandemic. The hospital is responsible for patients with moderate COVID-19 as well as patients with underlying diseases and mental illness and sets up COVID-19 patients with mental illness wards and intensive care unit (ICU) wards to admit critically ill patients.

### Participant recruitment

Participants will be recruited by physicians in the Gerontology Center of Zhongshan Hospital affiliated to Fudan University. Potentially eligible patients will be identified by trained physicians using an automated search and will receive a preliminary participant information sheet about the trial. Participants will be given a full explanation and time to consider before entering the trial, and if they agree, a written consent form will be signed. In addition, if the patient lacks the capacity to provide informed consent, a legal representative will be asked to provide consent. On the consent form, participants will be asked for their permission to share relevant data whether they withdraw from the trial or not. All written informed consent forms will be taken by a research nurse or a trained medical professional.

### Participant eligibility

Inclusion criteria are as follows:(1) Participants aged ≥ 18 years;(2) Participants with laboratory-confirmed SARS-COV-2 infection by reverse transcription PCR (RT-PCR);(3) Participants who are diagnosed with severe or critically ill COVID-19 according to the diagnosis and treatment protocol for COVID-19 patients (Trial Version 9) [19]. Table 1 lists the diagnostic criterion for severe or critically ill COVID-19 patients;(4) Contraception is maintained during treatment and for 90 days after the last dose of the study drug;(5) Participants (or legally authorized representatives) who sign the informed consent form before starting any procedure.

**Table 1 Tab1:** The diagnostic criterion for severe and critically ill COVID-19

Severe COVID-19 is defined as (no matter how long the condition lasts, at least one of the following conditions):
• Shortness of breath and respiratory rate ≥ 30 breaths/minute • Clinical symptoms progressively worsen, and lung radiographic infiltrates by imaging (eg, chest x-ray, CT scan.) show > 50% lung infiltrates within 24–48 h • PaO_2_) / (FiO_2_) ≤ 300 mmHg (1 mmHg = 0.133 kPa) • Oxygen saturation ≤ 93% in resting state
Critically ill COVID-19 is defined as (at least one of the following conditions):
• Respiratory failure (defined as the need to receive at least one of the following treatments according to local medical resources/conditions: endotracheal intubation and mechanical ventilation, high-flow nasal catheter oxygen supply (heating, humidification, enhanced nasal catheter oxygen supply, flow rate > 20 L/minute, oxygen supply ratio ≥ 0.5), positive pressure ventilation, ECMO, or clinical diagnosis of respiratory failure (defined as none of the above treatments cannot provide due to limited medical resources) • Shock (defined as systolic blood pressure < 90 mm Hg, diastolic blood pressure < 60 mm Hg, or the need for vasopressors) • Multiple organ dysfunction/failure

The diagnostic criterion for severe or critically ill COVID-19 patients can be adjusted according to the clinical diagnosis and treatment guidelines for COVID-19

Exclusion criteria are as follows:(1) Participants who have participated in other clinical studies of proxalutamide;(2) Anine aminotransferase (ALT)/aspartate aminotransferase (AST) > 5 times the upper limit of normal (ULN);(3) Serum total bilirubin > 1.5 × ULN;(4) Estimated glomerular filtration rate (eGFR) < 30 mL/min (including patients undergoing hemodialysis or hemofiltration);(5) Participants with suspected serious active bacterial, fungal, viral, or other infections (except infections of COVID-19), which may pose a risk when taking the study drug according to the opinion of investigators;(6) Participants with a known history of the human immunodeficiency virus (HIV), active hepatitis B, or active hepatitis C;(7) Pregnant or lactating women;(8) Participants with terminal underlying diseases who are not suitable for the study as assessed by the doctor;(9) Participants with a planned pregnancy within 90 days.

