### Intervention

Eligible patients will receive Proxalutamide (300 mg, Kintor Pharmaceuticals Ltd., Suzhou, China) plus standard of care. Proxalutamide will be administered orally once daily at the same time each day (± 2 h according to medication scheduling). The duration of the study treatment will last for 7 days and can be extended to 14 days at the discretion of the investigator.

Any dose that is missed and delayed may be administered as soon as possible on the same calendar day. When it is almost time for the next scheduled dose (within 4 h), we recommend skipping the missed dose and taking the next dose instead. The missed dose will not be made up if it is not given on the same calendar day.

Use of antipyretic medications (eg, paracetamol) or other adjunctive medications (eg, vitamins) is allowed before enrollment. Use of the following drugs is allowed during the trial period: treatment drugs against adverse events as well as underlying conditions (used stably for at least 3 months); oral contraceptive; convalescent plasma from recovered COVID-19 patients; anti–SARS-CoV-2 monoclonal antibodies; corticosteroids. Moreover, participants are advised to avoid the consumption of grapefruit, carambola, bigarade, or their juice, which belongs to CYP3A4 inhibitors and can increase exposure to proxalutamide. Allowable drugs for severe or critically ill patients with COVID-19 are administered based on investigators’ clinical judgment and clinical practice guidelines [20].

Discontinuance criteria of treatment are as follows: (1) If participants are tested negative for SARS-CoV-2 by RT-PCR assay or Ct values > 35, and repeated testing is still negative or Ct values > 35 after 24 h, the treatment will be discontinued by the investigator; (2) If grade 3–4 drug-related adverse events (AEs) occur during treatment, proxalutamide will be permanently discontinued.

It is important for the patient to fully understand the importance of conducting the trial, medicine administration on time, and follow-up on schedule during the trial for enhancing patient adherence. The subjects will be required to take the medicine according to the regulations, fill in the patient diary card on time, and attend the follow-up as required.

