### Study endpoints

The primary endpoint of this study is 30-day all-cause mortality. Secondary outcomes include the following:(1) 60-day all-cause mortality;(2) The proportion of clinical deterioration, which is defined as the need within 30 days after administration for admission to the intensive care unit or invasive mechanical ventilation/ extracorporeal membrane oxygenation (ECMO), or all-cause mortality;(3) Mean change in clinical status using the 8-point-ordinal-scale from day 1 (baseline) to day 15 and day 22 (optional);(4) Time to sustain clinical recovery (determined using an 8-point ordinal scale);(5) Percentage of subjects reaching sustained clinical recovery (determined using an 8-point ordinal scale) on days 5, 8, 15, and 22 (optional);(6) Mean change in the Acute Physiology and Chronic Health Evaluation II (APACHE-II) scores from day 1 (baseline) to days 15 and 22 (optional);(7) Changes in oxygenation index measured by blood gas analysis or blood oxygen saturation from day 1 (baseline) to days 3, 5, 8, 15, and 30 (optional);(8) Changes in chest CT scan (optional) from baseline to day 8 or 15;(9) Percentage of subjects confirmed negative for SARS-CoV-2 RT-PCR by nasopharyngeal (NP) swab on days 3, 5, 8, 15, and 30 (optional);(10) Change in Ct values of SARS-CoV-2 RT-PCR on days 3, 5, 8, 15, and 30 (optional);(11) Safety assessments (eg, AEs, serious AEs, and abnormal laboratory data) from the time of SARS-CoV-2 RT-PCR turned negative to day 30.

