The 8-point ordinal scale is an assessment of the clinical status at the first assessment of a given study day. The scale is defined as follows: (1) Death; (2) Hospitalized, on invasive mechanical ventilation or ECMO; (3) Hospitalized, on non-invasive ventilation or high flow oxygen devices; (4) Hospitalized, requiring supplemental oxygen; (5) Hospitalized, not requiring supplemental oxygen- requiring ongoing medical care (COVID-19 related or otherwise); (6) Hospitalized, not requiring supplemental oxygen, and no longer requires ongoing medical care; (7) Not hospitalized, limitation on activities; (8) Not hospitalized, no limitations on activities [21].

APACHE II score is a severity score and mortality estimation tool developed from a large sample of ICU patients, which consists of an acute physiology score (APS), the age of the patient, and chronic health points. And APACHE II score is made of 12 physiological variables and 2 disease-related variables. The maximum APACHE-II score is 71, though it is rare for a patient to score higher than 55. When APACHE II scores are combined with an accurate description of the disease, they can prognostically stratify acutely ill patients and assist investigators in comparing the success of new or differing forms of therapy [22, 23].

Nasopharyngeal swabs will be performed following a standardized procedure in this trial [24]. In addition, the result of NP SARS-CoV-2 RT-PCR will be adopted, if patients have already tested for NP SARS-CoV-2 RT-PCR no more than 48 h before the first drug administration. The viral clearance of COVID-19 in the treatment period defines as the results of both tests (the first test and retested 24 h later) being negative SARS-CoV-2 RT-PCR test or Ct values > 35.

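### Patients already negative or above Ct 35 at baseline can enter and be counted as negative in secondary endpoint (9), because neither eligibility nor the analysis sets set a virological baseline condition

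*Protocol article*

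**What the plan says.** All references are to the protocol article; no separate statistical analysis plan is shown.

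- **Participant eligibility.** Inclusion criterion (2) reads "Participants with laboratory-confirmed SARS-COV-2 infection by reverse transcription PCR (RT-PCR"). It has no Ct ceiling and no window for the test. None of the nine exclusion criteria, which begin with "Participants who have participated in other clinical studies of proxalutamide", concerns Ct, a negative swab or time since the positive test.
- **Follow-up and data collection.** Clearance rests on "the results of both tests (the first test and retested 24 h later"), each "being negative SARS-CoV-2 RT-PCR test or Ct values > 35". An existing result is accepted as the swab result for patients "tested for NP SARS-CoV-2 RT-PCR no more than 48 h before the first drug administration", whatever that result is. Table 2 makes a baseline swab mandatory.
- **Intervention.** The first discontinuance criterion uses the same threshold: "repeated testing is still negative or Ct values > 35 after 24 h, the treatment will be discontinued by the investigator".
- **Study endpoints.** Endpoint (9) is "Percentage of subjects confirmed negative for SARS-CoV-2 RT-PCR by nasopharyngeal (NP) swab on days 3, 5, 8, 15, and 30 (optional"). Endpoint (10) is the change in Ct on the same days.
- **Statistical analysis.** All efficacy results are analysed in the FAS and the per-protocol set. The FAS is defined by at least one dose and the per-protocol set by completing treatment without serious violation. Neither has a virological baseline condition.

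**The concern.** The entry criterion and the definition of virological success overlap. Because the clearance definition lists Ct above 35 as an alternative to a negative result, the protocol itself recognises results above 35 that are not reported as negative. A patient with such a result can satisfy inclusion (2). Because the confirming test has no time window, a patient whose baseline swab has already turned negative can also enter.

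Such a patient has nothing left to clear but remains in the denominator of endpoint (9), and can be in the numerator from the first post-baseline swab. In a controlled trial this would tend to affect both arms alike. Here there is no control arm. The Background and Discussion also cite faster viral clearance as an effect of the drug in milder disease, so the percentage negative is likely to be read as drug activity.

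The shared threshold adds a second oddity: a patient can enter at a value that, if repeated after 24 h, meets the criterion for ending treatment. That patient could be counted as negative after very little exposure.

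**Working it through.** **The plan's own figures.** The article gives no expected rate for viral clearance, so there is none to reproduce. Its one computed figure, 58 evaluable patients, concerns 30-day mortality. It reproduces with an exact binomial test of 12% against 2% at two-sided 0.05: success if at most 2 of 58 die, lower-tail error 0.0239, power 0.890. Nothing below changes it.

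**Step 1: can a patient past the threshold enter and be counted?**

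| Stage | Condition stated | Baseline Ct of 35 or below required? |
|---|---|---|
| Inclusion (2) | RT-PCR-confirmed infection | No |
| Nine exclusions | None virological for SARS-CoV-2 | No |
| Accepted earlier swab | Within 48 h before first dose | No |
| Clearance definition | Two tests 24 h apart, each negative or Ct above 35 | No |
| FAS | At least one dose | No |
| Endpoint (9) | Percentage of subjects negative by visit | No |

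No stage removes such a patient.

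**Step 2: does it depend on how endpoint (9) is read?** The endpoint does not cite the clearance definition.
- If negative in endpoint (9) includes Ct above 35, both baseline-negative patients and those entering above 35 can be counted.
- If only a reported negative counts, a patient at Ct 36 reported as positive is not counted. Baseline-negative patients still are.

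The gap exists under both readings and is wider under the first.

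**Step 3: size.** Let
- f = share of patients negative or above Ct 35 at baseline (not in the documents; assumed 5-30%, which is 3.2 to 19.2 of 64);
- r = share of those counted as negative at a given visit (not in the documents);
- q = true rate among patients with baseline Ct of 35 or below (not in the documents; illustrated at 20% and 50%).

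Observed rate = f·r + (1 − f)·q

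Inflation = observed − q = f·(r − q)

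With r = 1:

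| q | f = 5% | f = 30% |
|---|---|---|
| 20% | 0.05 + 0.95 × 0.20 = 24% | 0.30 + 0.70 × 0.20 = 44% |
| 50% | 0.05 + 0.95 × 0.50 = 52.5% | 0.30 + 0.70 × 0.50 = 65% |

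Each 10% of patients entering past the threshold adds 0.10 × (1 − q): 8, 6 or 4 percentage points at q = 20%, 40% or 60%.

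**Step 4: sensitivity to r and to the visit.**
- With r = 0.8 and q = 20%, the range is 0.05 × 0.8 + 0.95 × 0.20 = 23% to 0.30 × 0.8 + 0.70 × 0.20 = 38%.
- If r = q the inflation is zero; if r < q it is negative.
- With r = 1 and q = 90%, as might hold at a late visit, the inflation is only 0.05 × 0.10 = 0.5 to 0.30 × 0.10 = 3 points.

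**Step 5: should endpoint (10) be restricted in the same way?** Dropping patients above Ct 35 cuts off the upper tail of a noisy baseline. As an illustration, all assumed: baseline mean 30, total SD 5, within-patient SD 3. The cut at 35 lies 1 SD above the mean.
- Mean shift among those kept: 5 × 0.242 / 0.841 = 1.44 Ct below 30.
- Share of baseline variance that is within-patient: 9 / 25 = 0.36.
- Expected rise at follow-up with no true change: 0.36 × 1.44 ≈ 0.5 Ct.

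The restriction would create an apparent rise in Ct, with no control arm to reveal it.

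**The case against.** The strongest objection is that the link to endpoint (9) is inferred. The sentence beginning "The viral clearance of COVID-19 in the treatment period defines as the results of both tests" defines viral clearance, whereas endpoint (9) speaks of a confirmed negative RT-PCR. **This stands in part.** Such patients can be counted; the text does not establish that all of them will be. It does not remove the point, because the clearance definition is the only virological success definition in the article and baseline-negative patients are exposed under either reading.

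A reader might infer more: that these patients had cleared the virus before the first dose and are reported as conversions on treatment. The documents do not support that. Clearance needs two qualifying tests 24 h apart, so one entry value above 35 is not clearance. Endpoint (9) is a percentage negative by visit and is not described as conversion.

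A reader might also infer that the percentage is certainly inflated at every visit. **It is not certain.** The bias is upward only when r exceeds q, which is the expected case but not guaranteed, and it fades as q approaches 1. The laboratory's cut-off for reporting a positive is not given. If results above 35 are not reported as positive, fewer patients enter this way.

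Finally, denominators for responder summaries are commonly left to the analysis plan, the article is condensed, and only secondary virological endpoints in an exploratory trial are involved. **The low weight is fair.** But the article does fix the analysis sets for all efficacy results and gives them no virological condition, so the problem comes from what is stated rather than only from what is left out.

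**Conclusion.** The concern holds as a minor point on secondary endpoint (9). Eligibility, the clearance definition and the analysis sets, read together, allow patients already negative or above Ct 35 at baseline to be counted as negative in a trial with no comparator.

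The size cannot be known from the documents. The ranges in the working rest on an assumed f of 5-30% and on r = 1, which is the upper case. The expected direction is upward when r exceeds q, and the effect is largest at early visits, when few other patients have turned negative.

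It would be tempting to carry the same conclusion over to endpoint (10) and restrict both. That does not follow, because truncating on the baseline value introduces regression to the mean. Primary 30-day mortality and the sample size are not touched.

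**What to change.** The article reports that all 64 participants have been recruited, so the remedy lies in the analysis wording:

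1. State whether a confirmed negative in endpoint (9) uses the clearance definition (two tests 24 h apart, negative or Ct above 35) or a reported negative only.
2. Report endpoint (9) among FAS patients whose baseline swab is positive with Ct of 35 or below.
3. Give the number of patients negative or above Ct 35 at baseline.
4. Keep the all-FAS percentage as a supporting line.
5. Leave endpoint (10) in all FAS patients, shown alongside baseline Ct, and do not select on the baseline value.

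Separately, the investigators should reconcile the entry criterion with the threshold in the first discontinuance criterion. No clinical rule is proposed here.

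**Cost.** No new data are needed, because Table 2 already requires the baseline swab and endpoint (10) already needs its Ct. The price is a slightly smaller denominator for endpoint (9). If no patient entered past the threshold, the restricted and all-FAS results coincide and nothing is lost.

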### Sample size calculation

The primary endpoint of this study is the 30-day all-cause mortality. Based on a previous study, the all-cause mortality rate of hospitalized patients infected with COVID-19 is approximately 7.3% to 14.1% [25, 26]. Assuming that the proportion of all-cause mortality is 12% in severe or critically ill patients infected with COVID-19 under standard therapy, it is expected that the proportion of all-cause mortality can be reduced to 2% after treatment with proxalutamide. The probability of a type I error is set at 0.05 (*p* = 0. 05) with a power of 80%, and 58 patients will be required to be enrolled based on the exact probability method. It is expected that the drop-out rate of enrolled subjects will be ≤ 10%. Thus, this study is planned to recruit 64 severe or critically ill patients with COVID-19.

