Despite the above strengths, there are still some limitations in the present study. Firstly, our sample size was small and the trial was conducted at one center. However, as the COVID-19 pandemic is a sudden and temporary event, the center for accepting and treating severe or critically ill patients with COVID-19 is limited and temporally, meanwhile, the number of recruited severe or critically ill patients at clinical centers may be low. Secondly, this trial did not include a control group, therefore, reducing the generalizability of our results. Because there is no approved effective conventional treatment for patients with severe or critical COVID-19. Given the ethical considerations of protecting the maximum benefits of participants and the objectives (rapid discovery of proxalutamide efficacy) of this investigator-initiated clinical trial, no control group was recruited for this study. Randomized controlled trials will continue to be conducted in the future to assess the effect of proxalutamide. Thirdly, this is an open-label trial, considering severe or critically ill patients with COVID-19 may deal with invasive treatment delivered in the ICU (including ECMO), which is undoubtedly more difficult or impossible to conduct a blinded trial. But blind will be maintained for all other members of the clinical and research team, such as statistical staff, to minimize bias.

In summary, the present trial is the first to investigate the efficacy and safety of proxalutamide in severe or critically ill patients with COVID-19. The findings of this study might provide convincing evidence regarding the efficacy and safety of proxalutamide on severe or critically ill patients with COVID-19.

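### As worded, Table 1 lets a diastolic pressure below 60 mmHg alone make a PCR-positive patient critically ill; if such entrants die less often, the single-arm mortality falls without a drug effect

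*Protocol article*

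**What the plan says.** Under Participant eligibility, criterion (2) requires "Participants with laboratory-confirmed SARS-COV-2 infection by reverse transcription PCR (RT-PCR") and criterion (3) admits "Participants who are diagnosed with severe or critically ill COVID-19 according to the diagnosis and treatment protocol for COVID-19 patients (Trial Version 9"), with Table 1 given as the list of diagnostic criteria. For the critical class the table opens "Critically ill COVID-19 is defined as (at least one of the following conditions"). One of its three conditions is "Shock (defined as systolic blood pressure < 90 mm Hg, diastolic blood pressure < 60 mm Hg, or the need for vasopressors").

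A footnote to Table 1 allows the criteria to be adjusted to the clinical guidelines. None of the nine exclusion criteria refers to blood pressure.

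On the source population, Trial setting states "The hospital is responsible for patients with moderate COVID-19 as well as patients with underlying diseases and mental illness", and adds that ICU wards are set up for critically ill patients. Participant recruitment states "Potentially eligible patients will be identified by trained physicians using an automated search".

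The primary endpoint is 30-day all-cause mortality. Sample size calculation assumes that "the proportion of all-cause mortality is 12% in severe or critically ill patients infected with COVID-19 under standard therapy", to be reduced to 2% on the drug, and arrives at 58 patients, or 64 with drop-out. The Discussion acknowledges that "this trial did not include a control group". Trial status reports 64 participants recruited.

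**The concern.** The three elements of the shock definition are alternatives, and shock is itself one of several alternative conditions for critical illness. A patient at 125/58 mmHg with normal oxygenation therefore satisfies the wording. No respiratory criterion, low systolic pressure or vasopressor need has to be present as well. The label and the rule that assigns it do not match.

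In a randomised trial, a loose entry rule would affect both arms alike. Here the primary result is one percentage, read against a fixed 12%. If the rule admits patients at lower risk than the reference assumes, the percentage drops through case mix, and the drop looks like a drug effect. It would also weaken any statement about critically ill patients, which is the population the article says it informs.

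**Working it through.** **Step 1: logic of the rule.** Critically ill = respiratory failure OR shock OR multiple organ dysfunction. Shock = systolic < 90 OR diastolic < 60 OR vasopressors. So diastolic < 60 mmHg implies shock, which implies critically ill, and that meets the listed criteria for inclusion (3). Exclusions (5) and (8) are left to medical judgement and concern other infections and terminal disease, so they do not close this route.

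**Step 2: the plan's own figure.** Inputs from Sample size calculation: p0 = 0.12, p1 = 0.02, alpha 0.05, power 80%, exact method. Taking alpha as two-sided (0.025 in the lower tail), with X deaths in N patients:

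- N = 57: the largest allowed count is 1 death; P(X ≤ 1 | 0.12) = 0.006; power P(X ≤ 1 | 0.02) = 0.684.
- N = 58: the largest allowed count is 2 deaths; P(X ≤ 2 | 0.12) = 0.0006 + 0.0048 + 0.0185 = 0.0239; power P(X ≤ 2 | 0.02) = 0.890.

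So 58 reproduces as the smallest N with at least 80% power, and 58 × 1.1 = 63.8 gives 64. The sample size is not in dispute. The article does not state a cut-off of 2 deaths; it is the cut-off implied by 58 under this test.

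**Step 3: effect of dilution with no drug effect.** Let f be the share who qualify on diastolic pressure alone and m their 30-day mortality under standard care; the rest die at 12%. Neither f nor m is in the documents, so both are assumptions.

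Expected mortality: p = (1 − f) × 0.12 + f × m.

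For example, f = 0.20 and m = 0.02 give 0.80 × 0.12 + 0.20 × 0.02 = 0.096 + 0.004 = 0.100.

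The chance of an apparent success is P(X ≤ 2 | N, p):

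| f | m | p | N = 58 | N = 64 |
|---|---|---|---|---|
| 0 | – | 12.0% | 0.024 | 0.013 |
| 10% | 2% | 11.0% | 0.039 | 0.023 |
| 20% | 2% | 10.0% | 0.062 | 0.039 |
| 10% | 5% | 11.3% | 0.034 | 0.020 |
| 20% | 5% | 10.6% | 0.047 | 0.028 |
| 10% | 8% | 11.6% | 0.029 | 0.017 |
| any | 12% | 12.0% | 0.024 | 0.013 |

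At N = 64 a cut-off of 2 deaths starts from 0.013, so a 10% share at 2% mortality still leaves the probability below 0.025, while a 20% share does not. If m exceeds 12%, p rises above 12% and the bias works against the drug.

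**The case against.** The strongest reply is that entry depends on a diagnosis and not on a reading. Criterion (3) asks for a diagnosis of severe or critically ill COVID-19 under a cited guideline. The item is headed shock and sits under critically ill COVID-19, trained physicians identify the candidates, and the footnote lets the criteria follow guidelines. The guideline and the full protocol are not shown, so the bracketed wording may be a condensed translation. The hospital also has ICU wards for critically ill patients. This stands as a limit on what can be concluded. It does not remove the wording, because Table 1 is the rule that the article gives.

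A reader might infer that no link to COVID-19 is needed, or that a single passing reading suffices. The documents do not support either. The diagnosis itself is of COVID-19 illness, and the remark that duration is immaterial is attached only to the severe class; for shock the text is silent on duration.

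A reader might also infer that every such patient adds a low-risk survivor. That is an assumption. The documents give no mortality for this group, and patients with low diastolic pressure may be frail or unstable. The 2% used above is the plan's on-drug target and is not an estimate for these patients.

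Finally, the 12% is itself loosely matched: it rests on a range of 7.3% to 14.1% in hospitalised patients generally, while the Background cites 60.5% for critical cases. That is a separate matter, and removing a few patients would not cure it.

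**Conclusion.** The point holds as one about wording and its possible consequence. Table 1, as written, makes diastolic pressure below 60 mmHg sufficient for critical illness, and the uncontrolled design leaves the primary percentage open to any resulting change in case mix. Whether any patient entered this way, and whether such patients die less often than the rest, cannot be told from the documents.

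Under the illustrative 2% mortality, shares of 10% and 20% lower the expected percentage by 1 and 2 points. The chance of an apparent success then rises by a factor of about 1.6 and 2.6 at N = 58 (0.039/0.024 and 0.062/0.024). At N = 64 the factors are about 1.8 and 3, from a lower base of 0.013. The effect shrinks as the assumed mortality approaches 12% and vanishes there.

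It would go too far to say that the trial's mortality is biased. Nor does the point justify replacing the primary analysis population after recruitment is complete in an open-label trial, or removing these patients from the severity class that the table gives them.

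**What to change.** - From the screening records, where eligibility is already verified, record which Table 1 condition or conditions qualified each of the 64 patients.
- Keep 30-day mortality in the full analysis set as the primary result.
- Add one sensitivity analysis that leaves out patients whose only qualifying condition was diastolic pressure below 60 mmHg, and report how many there were and how many died. Fix this before the outcome data are examined.
- If the two results differ, temper any statement about critically ill patients accordingly.
- The sponsor should reconcile the term shock in Table 1 with its bracketed definition. No clinical threshold is proposed here.

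The cost is one data item, retrievable from existing records, and one extra analysis on a slightly smaller set. Recruitment and the primary analysis do not change.
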